### Phase 1.3 - product development and user testing (August 2018–August 2019)

Following design research and prototyping, we proceeded to develop our final intervention design in collaboration with a software development firm. Throughout this period, we engaged 237 users (85 boys, 87 girls, 23 parents or school administrators, and 51 pharmacists) in testing the emerging products through a combination of individual interviews and small group discussions, and developed a plan for implementing the products in schools and pharmacies. We iterated from low-fidelity prototypes such as paper mockups to realistic digital prototypes in order to incorporate user feedback on tone and voice of the content, visual design, characters and user flow through the website. We also considered how to improve user experience and reduce barriers to use. For example, we found that while many adolescents do not have their own smartphones, most have access to a device, and therefore we provided the option for youth to subscribe to SMS for a better order experience. In line with common practice in human-centered design, we ran multiple rounds of iterations in order to gauge users’ views on the look and feel of the products, and to ensure that they find the learning process fun, the content relevant, and the order process trustworthy.

### Phase 1.4 - content development and the theory of planned behavior (September–December 2019)

In the final stages of developing the intervention, based on an Intervention Mapping protocol [14], we mapped each CyberRwanda behavioral outcome to the Theory of Planned Behavior (TPB). We then used those outcomes to develop the key messages, determine how best to communicate those messages throughout program content and design and guide the evaluation. As a commonly used tool in understanding health behaviors, the TPB explains how determinants of behavior include (1) intentions to engage in that behavior and (2) perceived control over that behavior [7]. Figure 3 outlines the behavioral pathways suggested by the framework.

**Fig. 3 Fig3:**
[figure not shown]
Behavioral pathway leading to increased contraceptive use. Example behavioral pathway defined by the Theory of Planned Behavior, from knowledge to behavior change in usage of modern contraceptive methods

### Final intervention design

The final digital intervention design of CyberRwanda comprised a youth-facing web application^2^ and pharmacist training application. It is delivered through a school implementation model.^3^ A schematic of the intervention is displayed in Fig. 4.

**Fig. 4 Fig4:**
[figure not shown]
CyberRwanda Intervention Design. **a**: Schematic describing the components of the CyberRwanda digital intervention including the youth-facing web application and pharmacist portal; **b-e**: Images of the youth-facing web application pages [‘Home’ (**b**); ‘Learn’ (**c**); ‘Shop’ (**d**); ‘Ask’ (**e**)]; **f**: Image of the pharmacist portal. Images are the property of YLabs and published with permission of author and YLabs Executive Director [name]

#### Youth-facing web application

There are three main sections of the web application: Learn, Shop and Ask.

##### Learn

Users of CyberRwanda can access edutainment content on FP/RH and economic empowerment. The interactive webcomic follows the two main characters, Happy and Ganza, and their friends, as they navigate adolescence. Characters Mama and Nurse Keza offer advice on pressing health and life questions.

##### Shop

CyberRwanda facilitates the connection between users and local pharmacists who have been trained in providing youth-friendly care. Users can place orders for products such as sanitary pads, pregnancy tests, and contraceptive methods. When required for products such as emergency contraception, users answer medically relevant questions when ordering, and the responses are sent directly to the pharmacist. If they choose, they can enter a phone number to receive order updates via SMS. Online ordering allows youth to avoid uncomfortable interactions with a pharmacist to learn the required information about the products they are purchasing and enables them to collect their order quickly and discreetly from a pharmacist who they know is trained in youth-friendly care.

Young people pay for the products at market rate, with the cost set by the participating pharmacy and viewable on the Cyberwanda online shop. This means that young people are able to more easily ‘shop around’ for the pharmacy with the lowest price. At this stage of the program implementation, vouchers and/or subsidies are not provided for products, though this is a feature that could be feasibly integrated to the platform in future. While young people are able to obtain some products for free or lower cost at health facilities (and can search for these through the CyberRwanda facility finder), our research found that young people prefer to go to pharmacies to purchase products.

##### Ask

Over 200 frequently asked questions are available on the website and searchable by topic, with content written in an age-appropriate and accessible format. Content is aimed towards the lower range of expected users (12–15 years old). Age appropriateness is determined based on the UN International Technical Guidance on Comprehensive Sexuality Education (CSE), upon which the Rwanda Education Board’s CSE curriculum is based. Additionally, all content is validated by Rwanda’s adolescent health and sexual and reproductive health working groups.

#### Pharmacist training application

Pharmacists can elect to join the CyberRwanda network to be listed on the platform as a “youth-friendly” provider and fulfill orders through the site, increasing their potential customer base and revenue. Pharmacists who join the CyberRwanda network must complete training on topics relating to contraceptive methods, national guidelines on providing FP/RH care to adolescents, and how to deliver youth-friendly care. This is delivered through an in-person workshop that counts towards the pharmacists’ continuing professional development credits, as well as a scenario-based online training game.

To help ensure the majority of staff at each participating pharmacy are trained in the CyberRwanda process and providing youth-friendly care, both in-person and virtual training will be provided. Participating pharmacies will be given the option to send either the head pharmacist or nurse to in-person training, and a shorter virtual training will be provided for other staff at the pharmacy. Additionally, to address turnover or the opening of new pharmacies in our target areas, we will conduct refresher trainings.

#### CyberRwanda school implementation model

The CyberRwanda web application is introduced to adolescents in schools through one of two different models, facilitated and self-service, to test whether CyberRwanda requires intensive face-to-face programming in addition to online delivery in order to be effective. The primary difference between the two models is the resource-intensiveness of the implementation. The CyberRwanda self-service model is “lighter-touch,” delivered in schools without peer facilitation and guidance for engaging with the content. A launch event is held at the school to promote the program. Concurrently, training is given to teachers and selected students (“student ambassadors”), along with the provision of tablets and a preloaded internet hotspot, to help students access CyberRwanda during their free time. In contrast, the facilitated version is a more labor-intensive, interactive experience, and potentially effective in response to the insight from prototyping that youth have stronger engagement when learning from and with their peers. In addition to all of the components of the self-service model, the facilitated model also introduces CyberRwanda through school clubs in which trained students (“peer facilitators”) work through an activity booklet and curriculum that accompanies the online material in weekly sessions with their fellow students.

In both the facilitated and self-service implementation models, students interact with CyberRwanda through provided tablets which are connected to the internet. The schools have a degree of discretion over how the tablets are able to be accessed, based on school facilities and programs, supervisory teachers’ capacity, peer facilitators’ preferred modes of engagement, and the school’s preferences. Guidance from the CyberRwanda team mandates a minimum of 5 h/week of access to the tablets, which can be both in unstructured time (e.g. access from the library during lunch hours or after school) and structured time (e.g. classes in which students can access the tablets). Students can also access the tablets via the teachers or from the peer facilitators. Any student in the school is able to access the tablets, not just those who are participating in the study. To overcome the potential barrier of poor internet connectivity in the school, a wifi hotspot with good nation-wide coverage is provided for exclusive use on the CyberRwanda application. A native app is also being developed to allow for future offline use on CyberRwanda tablets, in the case of disruptions in connection.

There is a potential risk of spillover in that students exposed to CyberRwanda may access it on personal phones or tablets outside of the program, and could feasibly share it with friends in non-participating or control schools. Evidence on usage of CyberRwanda from the pilot program suggests that students are unlikely to share CyberRwanda with their friends or attempt to access it outside of school, and the geographical distance between treatment and control schools is intended to minimize the potential for sharing to occur between control and treatment groups.

### Phase 2: implementation and evaluation

Phase 2 includes the implementation and 24-month evaluation of CyberRwanda, which is set to commence in 2020, following in-person school reopening after the COVID-19 crisis.

#### Aims

The study objective is to determine if CyberRwanda can significantly improve health outcomes among youth aged 12–19 as measured through uptake of modern contraceptive methods, delayed initiation of childbearing and increased HIV testing. The secondary objectives are to measure the impact of the CyberRwanda intervention on a set of outcomes related to FP/RH in the following areas: knowledge, behavioral intentions, self-efficacy, social norms and engagement in employment, education, and training.

We are also preparing a cost-effectiveness evaluation to measure the relative cost-effectiveness of the two different implementation models, which will be the subject of a separate protocol.

#### Outcomes

The primary outcomes, measured at the individual participant level, are:
Uptake of a modern method of contraception (ages 15–19): The proportion of youth who report currently using a modern method of contraception at endline (24 months)Initiation of childbearing (ages 15–19): The proportion of youth who report having ever been pregnant or fathered a pregnancy at endline (24 months), regardless of the pregnancy outcomeHIV testing (ages 12–19): The proportion of youth who have ever had an HIV test at endline (24 months).

While the intervention will be available to 12–19-year-olds at study intervention schools, the first two primary outcomes are measured for 15–19-year-olds for two main reasons: 1) sample size would need to be increased substantially to have sufficient statistical power to detect an effect in the younger age group; and 2) stakeholders were more comfortable focusing the evaluation outcomes on older adolescents to align with social expectations on talking about sexuality. HIV testing is not as stigmatized according to age, because it is routinely conducted irrespective of sexual activity.

Secondary outcomes include the following, measured at the individual participant level for participants aged 15–19 at endline (24 months):
Level of knowledge of contraceptive methods and how to prevent pregnancyBehavioral intentions to use contraceptives, pregnancy intentions, intent to discuss contraceptives with partnerSelf-efficacy related to family planning and reproductive healthSocial norms related to contraceptive use and other reproductive health behaviorsEngagement in employment, education and training: proportion of youth currently in school, training or employment.

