CyberRwanda is a digital intervention for urban and peri-urban youth aged 12–19. Designed in partnership with youth and their communities, it combines age-appropriate storytelling content about FP/RH and economic empowerment, with discreet, streamlined access to contraception and other essential products from trained pharmacists through a mobile ordering platform. Through CyberRwanda, young people can order products online for discreet in-person collection at participating pharmacies, after answering medically-relevant questions and reading information about the products online. All participating pharmacies are trained on the provision of youth-friendly care. CyberRwanda addresses the challenges adolescents face in finding and accessing accurate information on socially taboo topics, locating youth-friendly care, and then discreetly ordering and receiving products. Co-designed with healthcare providers, accompanying training tools for pharmacists support them to provide youth-friendly care.

The objective of CyberRwanda is to improve a spectrum of adolescent health outcomes, with specific focus on increased uptake of modern contraception, delayed initiation of childbearing, and increased rates of HIV testing. Within a Theory of Planned Behavior (TPB) framework [7], we hypothesize that CyberRwanda will strengthen the knowledge, attitudes, perceived social norms, and perceived behavioral control of participants, leading to the aforementioned health outcomes.

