#### Sample size calculations

The sample size was determined for the primary outcome of uptake of a modern contraceptive method. Power and sample size analyses were conducted for the primary analysis using 2000 simulated datasets (created in R statistical software) constructed based on historic data on the proportion of sexually active youth currently using a modern contraceptive method.

The primary analysis is powered at 80% to detect the presence of an intervention effect when CyberRwanda facilitated has a relative risk of at least 2.5. Although this relative risk seems large, in absolute terms, the baseline percentage of girls using contraception is only 2%, so this would mean increasing that to 5%. To achieve this power, we need to enroll 60 schools and 50 girls per school (equal cluster size is assumed). When we include boys (who are not part of the primary outcome on which the study is powered), this means we will enroll a total of 100 students per school, for a total of 6000 students in the study.

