#### Data analysis

To first assess the presence of an intervention effect, we will utilize a generalized linear mixed model (GLMM) with uptake of a modern contraceptive method (binary outcome) and initiation of childbearing (binary outcome) as the outcome variables. The model will include a binary explanatory variable for the intervention group (control vs. CyberRwanda in either the self-service or facilitated arm) with control group as the reference, and model terms for the stratification factor (district) as well as other relevant variables measured at baseline (e.g. age, sex). We will present relative risks and 95% confidence intervals using robust standard errors to account for clustering at the school and district levels.

If there is evidence of a statistically significant intervention effect relative to control, we will proceed with the assessment of non-inferiority to understand whether CyberRwanda self-service is non-inferior to CyberRwanda facilitated within a specified margin. To do this, the coefficients on the categorical variable for the intervention groups can be used as approximations of the log relative risks (RRs) comparing the probability of contraceptive uptake (or initiation of childbearing) in the intervention arms compared to control arm. We will use a one-sided Wald-style test of non-inferiority, based on an a priori specified non-inferiority margin of 50% of the lower bound of the confidence interval for CyberRwanda facilitated.

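### The HIV-testing primary outcome counts tests done before the programme, which dilutes the effect by the share of students already tested at baseline

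*Protocol article*

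**What the plan says.** The Outcomes section lists three primary outcomes. The third, for ages 12–19, is "The proportion of youth who have ever had an HIV test at endline (24 months"). It has no look-back period, no limit to tests after baseline and no restriction to students untested at entry. The eligibility criteria do not exclude students who have been tested before.

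The Background gives the programme's focus as "increased uptake of modern contraception, delayed initiation of childbearing, and increased rates of HIV testing", and the Aims section likewise speaks of increased HIV testing. To explain why this outcome covers the younger ages too, the Outcomes section says that HIV testing carries less age-related stigma, "because it is routinely conducted irrespective of sexual activity". No baseline proportion tested is given anywhere.

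On size, "The sample size was determined for the primary outcome of uptake of a modern contraceptive method". No rate, effect or power is stated for HIV testing. Surveys are planned at baseline, at 9–12 months and at 24 months in the same cohort.

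**The concern.** The aim is a change in testing brought about by the programme, but the endpoint is a lifetime status. A student tested before baseline is fixed as a success in every arm, and a later test in that student cannot register. Only students untested at baseline can show an effect, yet all students stay in the denominator.

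This is one of three primary outcomes. A real rise in testing over the 24 months could appear as a small relative risk with a wide interval, and be read as the programme having failed to increase testing. The remark that testing is routine gives reason to expect that some students will already have been tested, though it does not say how many.

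**Working it through.** **The plan's own figure.** The only power statement is for contraception: "powered at 80% to detect the presence of an intervention effect when CyberRwanda facilitated has a relative risk of at least 2.5", which is 2% versus 5% among girls in 60 schools × 50 girls = 3000. It came from simulation and no ICC is printed. An approximate check (two proportions, two-sided 5%, no attrition) gives exactly 80% at an ICC of about 0.024 for 20 control versus 40 intervention schools, or about 0.014 for 20 versus 20. The figure is attainable and is not questioned here. There is no corresponding figure for HIV testing to reproduce.

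**Inputs from the article.** 60 schools and 6000 students, so 100 per school (Sample size calculations). 10% attrition, so 90 per school (Student follow-up). Control versus both intervention arms combined, with 95% confidence intervals (Data analysis), from which a two-sided 5% level is inferred.

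**Assumptions not in the article.** Equal allocation, giving 20 × 90 = 1800 control and 40 × 90 = 3600 intervention students. Probability of a new test among the untested: 20% control, 28% intervention. ICC 0.03, with 0.01 as an alternative. b from 5% to 60%.

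**Dilution.** With q the 24-month probability of a first test among the untested:

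- Ever-tested at endline = b + (1−b)q
- Risk difference on ever-tested = (1−b) × (28% − 20%)

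**Power.** Power = Φ(RD/SE − 1.96), with the unpooled variance multiplied by the design effect 1 + (m−1) × ICC. Worked at b = 20%, ICC 0.03:

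- *Ever-tested.* Rates 0.20 + 0.80 × 0.20 = 0.360 and 0.20 + 0.80 × 0.28 = 0.424. RD 0.064, RR 1.18. Design effect 1 + 89 × 0.03 = 3.67. SE = √[3.67 × (0.360×0.640/1800 + 0.424×0.576/3600)] = 0.0268. z = 2.39, power 67%.
- *First test among the baseline-untested.* 1440 versus 2880 students, 72 per school. RD 0.08, RR 1.40. Design effect 1 + 71 × 0.03 = 3.13. SE = √[3.13 × (0.20×0.80/1440 + 0.28×0.72/2880)] = 0.0238. z = 3.36, power 92%.
- *Ever-tested adjusted for baseline status (approximate).* Students already tested have no remaining variance, so the residual variance is (1−b)q(1−q). SE = √[3.67 × (0.80×0.16/1800 + 0.80×0.2016/3600)] = 0.0206. RD 0.064, z = 3.10, power 87%.

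| b | RR, ever-tested | Power, ever-tested (ICC 0.03) | Power, ever-tested adjusted (ICC 0.03) | Power, first test in untested (ICC 0.03) | Power, ever-tested (ICC 0.01) |
|---|---|---|---|---|---|
| 5% | 1.32 | 88% | 92% | 93% | 99% |
| 10% | 1.26 | 81% | 91% | 93% | 98% |
| 20% | 1.18 | 67% | 87% | 92% | 91% |
| 40% | 1.09 | 41% | 77% | 89% | 68% |
| 60% | 1.05 | 24% | 59% | 84% | 42% |

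**Would counting any test since baseline do as well?** Take 20% versus 30%, ICC 0.03 and a pooled-variance test. If the programme raises testing equally in students tested before, power is 98.7% at every b. If it does not change testing in those students (20% in both arms), power is 96.7%, 84.5%, 57.2% and 25.4% at b = 10%, 30%, 50% and 70%. Ever-tested gives 93.5%, 71.7%, 46.7% and 26.1%. At high b the gain disappears. First tests among the baseline-untested keep 98.5%, 97.8%, 96.1% and 90.7%.

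**The case against.** The strongest reply is that b is unknown. The sentence about routine testing explains an age range and gives no rate, and the cohort is drawn from the first two secondary grades. At b = 5% the loss is only 88% against 93%, and at ICC 0.01 it is smaller still. That stands: the direction is certain from the definition, the size is not. A reader might infer that most students are already tested at entry. The article does not support that.

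Second, the model allows other relevant baseline variables and gives age and sex only as examples, so baseline testing status could be included without contradicting the text. That also stands, and the table shows adjustment recovering much of the loss. But the article does not commit to it, and adjustment recovers less than the first-test definition as b grows.

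Third, ever-tested is a legitimate measure of coverage. It is, but the stated aim is "increased rates of HIV testing", and in a cohort with a baseline survey a measure of new testing is within easy reach.

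Three stronger readings should be set aside.

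- *Bias.* Randomization balances b across arms in expectation, so this is dilution and lost power, not a route to a false positive.
- *Childbearing.* The ever-pregnant outcome might seem to share the flaw, but the aim there is delayed initiation, which an ever-measure captures directly, and the article gives no prevalence from which to argue otherwise.
- *The outcome list in Data analysis.* It names contraception and childbearing but not HIV testing. That is a separate matter and is not evidence for this point.

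**Conclusion.** The point holds as a loss of effect size and power on one of three primary outcomes. The risk difference shrinks by the factor (1−b) by construction. Under the stated assumptions (20% versus 28%, 1800 versus 3600 students, ICC 0.03), the loss against the first-test outcome runs from about 5 percentage points of power at b = 5% to about 60 at b = 60%, and it is milder at ICC 0.01. The rates, ICC, equal allocation and b are assumptions. A reader might infer that the trial's 80% power is wrong. It is not contradicted, because it concerns contraception only. The change should be made, since it is cheap and the loss could be large, but the trial does not fail without it.

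**What to change.** Confirm that the planned baseline survey records whether each student has ever had an HIV test, and add the item if it does not. Define the primary outcome as a first HIV test by endline among students never tested at baseline. This needs only the baseline and endline ever-tested answers, with no dated recall, and because the subset is fixed by a baseline answer the arms stay comparable. At minimum, keep ever-tested and name baseline ever-tested status as a covariate in its model.

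The cost is a wording change before launch, possibly one survey item, and a registry outcome update. The downside is small: the first-test outcome describes only students untested at baseline and does not count retests. Ever-tested can be kept as a supporting measure of coverage.
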